# TRial to Assess Implementation of New research in a primary care Setting (TRAINS): study protocol for a pragmatic cluster randomised controlled trial of an educational intervention to promote asthma prescription uptake in general practitioner practices

**DOI:** 10.1186/s13063-022-06864-y

**Published:** 2022-11-17

**Keywords:** Asthma, Child, Childhood asthma, Asthma management, Cluster randomised controlled trial, GP practices, Public health intervention, Knowledge Translation, Knowledge Mobilisation, Implementation, Prescription pattern, Unscheduled medical contacts

## Abstract

**Background:**

There is a marked increase in unscheduled care visits in school-aged children with asthma after returning to school in September. This is potentially associated with children not taking their asthma preventer medication during the school summer holidays. A cluster randomised controlled trial (PLEASANT) was undertaken with 1279 school-age children in 141 general practices (71 on intervention and 70 on control) in England and Wales. It found that a simple letter sent from the family doctor during the school holidays to a parent with a child with asthma, informing them of the importance of taking asthma preventer medication during the summer relatively increased prescriptions by 30% in August and reduced medical contacts in the period September to December. Also, it is estimated there was a cost-saving of £36.07 per patient over the year. We aim to conduct a randomised trial to assess if informing GP practices of an evidence-based intervention improves the implementation of that intervention.

**Methods/design:**

The TRAINS study—TRial to Assess Implementation of New research in a primary care Setting—is a pragmatic cluster randomised implementation trial using routine data. A total of 1389 general practitioner (GP) practices in England will be included into the trial; 694 GP practices will be randomised to the intervention group and 695 control group of usual care. The Clinical Practice Research Datalink (CPRD) will send the intervention and obtain all data for the study, including prescription and primary care contacts data. The intervention will be sent in June 2021 by postal and email to the asthma lead and/or practice manager. The intervention is a letter to GPs informing them of the PLEASANT study findings with recommendations. It will come with an information leaflet about PLEASANT and a suggested reminder letter and SMS text template.

**Discussion:**

The trial will assess if informing GP practices of the PLEASANT trial results will increase prescription uptake before the start of the school year. The hope is that the intervention will increase the implementation of PLEASANT work and then increase prescription uptake during the summer holiday prior to the start of school.

**Trial registration:**

ClinicalTrials.gov ID: NCT05226091

**Supplementary Information:**

The online version contains supplementary material available at 10.1186/s13063-022-06864-y.

## Background

Asthma is a chronic respiratory disease that affects adults and children. It is a disease of the airways that results in inflammation and narrowing of airways associated with wheezing, coughing and shortness of breath [1]. According to Asthma UK, approximately 5.4 million people in the UK have asthma, 4.3 million adults [1 in 12] and 1.1 million children [1 in 11] [2]. Asthma is the most common chronic disorder that affects children worldwide [3]. The National Review of Asthma Deaths (NRAD) reported that 45% of people who died from asthma between 2012 and 2013 could have been prevented [4]. Worldwide, children in the UK suffer from the highest prevalence of asthma symptoms. Every 20 min, a child in the UK is hospitalised from an asthma attack, and 185 Adults and children are admitted every day [5].

People with asthma should be assessed, and their medications should undergo a continuous assessment to manage their disease and reduce the disease burden [6]. In the UK, the National Institute of Health and Care Excellence (NICE) recommends that patients with asthma should be followed up at least once a year to determine whether their treatment needs to be modified [7]. According to current clinical guidelines by the British Thoracic Society (BTS) and NICE, all individuals who have been hospitalised with an asthma attack should receive a follow-up assessment in primary care within two working days of discharge to evaluate asthma control and ensure symptoms are resolved. Despite this, 64% of respondents to the 2018 National Asthma Survey did not follow-up with their GP after an attack, and many patients were unaware this was required [7, 8].

Non-adherence to asthma medication or inhaler mishandling increases morbidity, mortality, and hospital admission [9]. Previous work by our research group has shown that school-aged children with asthma are twice as likely to have an unscheduled care contact after returning to school in September as children without. Furthermore, 30% will have an unplanned medical visit in the month of September [10]. The increase in unscheduled contacts is associated with a drop in the number of asthma-related prescriptions for preventer medications during the preceding summer holidays (Fig. 1) [11].

**Fig. 1 Fig1:**
[figure not shown]
Number of asthma preventer prescription uptake by month in England [11]

This research provided the rationale for the PLEASANT study (*P*reventing and *L*essening *E*xacerbations of *A*sthma in *S*chool-age children *A*ssociated with a *N*ew *T*erm) [12]. PLEASANT was a cluster randomised trial to assess whether a letter sent from a GP practice at the start of the summer vacation reminding parents of children with asthma of the necessity of continuing to take their medication during the summer holidays. The study evaluated whether the letter increased prescriptions in August and reduced unscheduled contacts after returning to school in September [13].

The PLEASANT study included 1279 school-age children from 141 general practices (71 on intervention and 70 on control) in England and Wales. Accordingly, the results of PLEASANT showed that the letter relatively increased prescription uptake in August by 30%—an absolute increase of 4% (Fig. 2)—and reduced the unscheduled medical contacts after the return to school the period September to December (Fig. 3). Although the effects were small the intervention was cost-saving—saving £36.07 per patient over 1 year [14].

**Fig. 2 Fig2:**
[figure not shown]
Prescriptions uptake over two years [14]

**Fig. 3 Fig3:**
[figure not shown]
Unscheduled contacts over two-years [14]

The PLEASANT trial showed that a simple, cost-effective intervention could increase preventer prescriptions and reduce unscheduled primary care contacts. There is, thus, a clear clinical benefit in translating the results of this clinical research from publication to practice. This leads to the motivation for the TRAINS project.

The TRAINS trial will assess the effect of an intervention sent to GP practices (Fig. 4). The intervention will provide information on the PLEASANT trial results and be sent by email and mail to the asthma lead and/or practice manager.

**Fig. 4 Fig4:**
[figure not shown]
A logic model for the TRAINS trial

### Primary research aim

The aim of this trial is to assess if informing GP practices about the findings of PLEASANT increases prescription uptake in school-age children with asthma. The primary objective of the trial is to determine whether the intervention increases asthma prescription uptake in children with asthma in August and September.

### Research question

This project will address the following research question:

“Does Informing General Practitioners about the Results of PLEASANT Trial Prevent Summer Holiday the Drop in Prescription Uptake by the Parents/Carers of School-Age Children with Asthma?”

### Rationale

The PLEASANT trial showed that a simple postal intervention effectively improves asthma outcomes in children in primary care. The objective of the current study is to conduct a randomised trial to assess if informing GP practices of an evidence-based intervention results in the implementation of that intervention.

## Methods and analysis

### Trial design

TRAINS will be a cluster randomised controlled parallel-group trial using routinely collected data. There are approximately 1389 general practices contribute to CPRD Aurum database in England. Six hundred ninety-four GPs will be randomised to the intervention group and 695 to the control group of usual care (Fig. 5). Data will be extracted over a 6 months period after the implementation. Cluster randomisation was chosen as the intervention will be delivered at the level of the practice.

**Fig. 5 Fig5:**
[figure not shown]
Trial summary

### Designing the intervention

The intervention (letter) has been designed through four phases based on five steps: an initial meeting with GPs, systematic review, trial steering committee, follow-up GP meeting, and a communication consultant (Fig. 6).

**Fig. 6 Fig6:**
[figure not shown]
Flowchart of the development of the intervention over time

In the first phase of designing the intervention, we conducted a seminar meeting with the Academic Unit of Primary Care in Sheffield to understand what design and content attributes are perceived by GPs. Then, we conducted a systematic review to ensure the study had not been done and to help develop the intervention. Based on the seminar recommendations and the systematic review results, two draft intervention templates were designed in September 2020. A long version and a short version. The long version included graphs from the PLEASANT study results alongside detailed text and the original reminder letter that was used in the PLEASANT trial. The short version included text but did not include graphs and links to download the PLEASANT’s reminder letter.

In the second phase of the design, we founded a trial steering committee and carried out a second seminar meeting to get feedback on the first two templates (long and short). Following this, recommendations were as follows: to send the short version of the intervention, to target the asthma clinical lead and practice manager, and to include a reminder letter and SMS text template to simplify and increase the possibility of the implementation. In addition, it was advised to attach a leaflet about PLEASANT Trial to support the letter and provide a link to the PLEASANT trial website for further details on PLEASANT and its publications and documents.

In the third phase of design, we contacted a communication and copywriting consultant, who has written extensively for both NHS England and Leicester City’s Public and Patient magazine, to enhance the language and layout of the intervention letter [15]. The short letter with a leaflet and suggested reminders (letter and SMS text for GPs to use) was shown to the communication consultant. The consultant edited the material to provide punchy and persuasive messaging for a series of communication interventions by letter, email, and leaflet. In addition, guidance was delivered on a high-impact visual layout and style of the letters and leaflet.

In the fourth phase of the design, the final version of the intervention was designed in April 2021. The intervention consists of a letter to GPs with recommendations and links, a supported leaflet about the PLEASANT study for more information about the findings, reminder templates for GPs to use and make it easier for implementation, and an email to GPs with the intervention materials. The final version of the intervention can be found in the supplemental material (Additional file 1).

### The intervention

Selected GP practices currently registered with CPRD and randomised to the intervention arm will receive correspondence twice, once by email and once by mail. The intervention is a letter that highlights the drop in prescription uptake for children with asthma during the summer holidays and introduces the results of the PLEASANT trial. In addition, it advises GP practices on the effect of reminding parents of children with asthma to continue taking their asthma preventer medications during the summer holidays. It will be sent with the assistance of the CPRD to the CPRD contact lead at GPs along with the named to the practice manager and asthma lead. The plan, subject to confirmation and amendment, is that the intervention will be sent by July 2021, which is the advice from the trial steering committee (TSC). Given the timing of the intervention, the hope is that GP practices will then send their correspondence to parents during the school holidays. It is hoped the intervention can be timed to enable sufficient time for GP practices to implement the advice from the intervention.

As this is an implementation study, the correspondence to GP practices is advisory, and the decision on implementation is down to the individual GP practices.

### Primary outcome measure

The proportion of children with asthma who have a prescription for an asthma preventer medication from 1 August 2021 to 30 September 2021.

### Secondary outcome measures

The number of asthma preventer medication prescriptions per school-aged child with asthma patient from 1 August 2021 to 30 September 2021The number of prescription uptake of asthma preventer medication per patient in the month of August 2021The number of prescription uptake of asthma preventer medication per patient in the month of September 2021The proportion of children who have a prescription for asthma preventer medication per patient in the month of August 2021The proportion of children who have a prescription for asthma preventer medication per patient in the month of September 2021The number of prescription uptake of asthma preventer medication in the 6 months following the intervention 1 July 2021The proportion of patients with unscheduled medical contact from 1 September 2021 to 31 December 2021 and the individual months of 1 September 2021 to 31 December 2021The number of unscheduled medical contact per patient from 1 September 2021 to 31 December 2021 and the individual months from 1 September 2021 to 31 December 2021The proportion of patients with a medical contact (either unscheduled or scheduled) from 1 September 2021 to 31 December 2021 and the individual months from 1 September 2021 to 31 December 2021The total number of medical contact (either unscheduled or scheduled) per patient in the period 1 September 2021 to 31 December 2021 and the individual months of 1 September 2021 to 31 December 2021The proportion of patients who have an unscheduled medical contact in the period 1 September 2021 to 31 December 2021 and the individual months of 1 September 2021 to 31 December 2021 associated with a respiratory diagnosisThe number of unscheduled medical contacts per patient and from 1 September 2021 to 31 December 2021 and the individual months of 1 September 2021 to 31 December 2021 associated with a respiratory diagnosis

### Setting and site recruitment

The study will be conducted within GP practices in England that are currently contributing to CPRD Aurum database. The GP practices will be randomised to receive the intervention, and they will not be aware that they are in the study. Approximately 1389 sites are expected to be involved in this trial based on current active CPRD GP practice sites.

### Randomisation and allocation concealment

Practices will be allocated 1:1 to intervention or control to ensure an equivalent sample size in each arm of the study in terms of the number of children with asthma. The randomisation will be stratified by the size of the practice as assessed by decile within the CPRD. All the practices in the study will be known from the CPRD and will not be prospectively recruited. GP practices randomised to the intervention will receive a postal bulletin and an email advising them to implement the study. GP practices randomised to control will not receive postal bulletin or email, and they will continue with usual care.

For practices included in the study, randomisation will be undertaken by study statistician using bespoke Excel spreadsheet. A file with anonymous practice identification codes and the stratification number will be provided to the CPRD. The statistician will not receive any information that would identify the practices.

### Population

The target population for the intervention will be general practices who are currently contributing to CPRD in England.

### Practices inclusion criteria

General practices who are currently contributing to CPRD Aurum database in England on or before the intervention were included.

### Practice exclusion criteria

General practices that are not in England, practices that leave CPRD after the intervention and before the end of follow-up, and practices that merge after the intervention and before the end of follow-up (where the merging practices were in different study arms) were not included.

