#### Data analysis

Statistical methods appropriate to a cluster randomised trial will be used for the analysis of the data. The statistical analysis will be performed on an intention-to-treat-basis and reported according to CONSORT guidelines for Cluster RCTs [17]. A dropout of practices is not expected. Some practices may merge, close, or split. Small numbers are likely to be involved, but no special treatment is necessary and no imputation is planned.

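### Practices are excluded for leaving CPRD or merging across arms after allocation, up to the end of follow-up, which conflicts with the intention-to-treat analysis and outlasts the primary window

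*Protocol article*

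**What the plan says.** Under Practice exclusion criteria, the Protocol article leaves out "practices that leave CPRD after the intervention and before the end of follow-up". It also leaves out practices that merge in that period, but only "where the merging practices were in different study arms) were not included".

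Under Data analysis it states: "The statistical analysis will be performed on an intention-to-treat-basis". The same paragraph adds "A dropout of practices is not expected", allows that some practices may merge, close or split, and concludes: "Small numbers are likely to be involved, but no special treatment is necessary and no imputation is planned".

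Three other sections set the timing and the randomised set:
- Randomisation and allocation concealment: "All the practices in the study will be known from the CPRD and will not be prospectively recruited". The full list of randomised practices therefore exists at allocation.
- Primary outcome measure: the outcome is the proportion of children with a "prescription for an asthma preventer medication from 1 August 2021 to 30 September 2021".
- Trial design: "Data will be extracted over a 6 months period after the implementation". The medical-contact outcomes under Secondary outcome measures run to 31 December 2021.

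The article defines no modified intention-to-treat set that would reconcile the exclusions with the analysis statement.

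**The concern.** Whether a practice will leave CPRD or merge cannot be known at randomisation, and the merger rule depends on the allocation itself. These are therefore not eligibility criteria. They remove randomised clusters because of later events, which an intention-to-treat analysis is meant to prevent.

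The timing adds a separate fault. One exclusion period, set by the longest secondary outcome, governs every analysis. Membership of the primary analysis thus depends on what happens to a practice in October to December, after its primary outcome is complete.

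At stake is the definition of the primary analysis population. The Trial status section says the data have arrived and are being cleaned. If the two statements stay as they are, the analyst must choose between them with the data in hand.

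**Working it through.** **1. The statements side by side**

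| Event after dispatch | Practice exclusion criteria | Data analysis | Compatible? |
|---|---|---|---|
| Leaves CPRD | Excluded | Intention to treat; no dropout expected | No |
| Merges with a practice in the other arm | Excluded | Intention to treat; no special treatment | No |
| Merges with a practice in the same arm | Kept | No special treatment | Yes |
| Splits, still contributing data | Not mentioned | No special treatment | Yes |

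The conflict is confined to the first two rows.

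**2. How much of the exclusion period follows the primary window**

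The end of follow-up is taken as 31 December 2021, the last date of any contact outcome. The start is not fixed: the Abstract gives June 2021, the section on the intervention says by July, and one secondary outcome counts from 1 July.
- Days after the primary window, 1 October to 31 December: 31 + 30 + 31 = 92.
- Start 1 July: the period is 184 days, and 92/184 = 50%.
- Start 15 June (an assumed mid-June date): the period is 200 days, and 92/200 = 46%.

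These are shares of calendar time. They become shares of leavers only if the leaving rate is constant, which is an assumption.

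**3. Precision**

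Inputs from Sample size: 694 and 695 practices, 85 children per practice, a rate of 30%, an intraclass correlation of 0.03.
- Design effect = 1 + (85 − 1) × 0.03 = 3.52.
- Half-width = 1.96 × √[0.30 × 0.70 × 3.52 × (1/(694 × 85) + 1/(695 × 85))] = 0.98 percentage points.

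This reproduces the stated 1%, read as the half-width for the difference between arms. It uses all 1389 practices, with no allowance for exclusions. Losing a fraction f from both arms divides the information by 1/(1 − f). The article gives no f, so a range is assumed:

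| Practices lost | Number | Half-width (points) |
|---|---|---|
| 0% | 0 | 0.98 |
| 1% | 14 | 0.99 |
| 2% | 28 | 0.99 |
| 5% | 69 | 1.01 |
| 10% | 139 | 1.03 |

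**4. Bias**

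Let f be the fraction excluded in an arm and d the uptake in retained practices minus that in excluded ones. The retained mean exceeds the arm's full mean by f × d. The difference between arms therefore shifts by f₁d₁ − f₀d₀, or (f₁ − f₀) × d if the gap is the same in both arms. The article gives neither f nor d; all values below are assumed.
- 5% in both arms, same 10-point gap: 0.
- 5% vs 3%, 5-point gap: 0.02 × 5 = 0.1 points.
- 5% vs 2%, 10-point gap: 0.03 × 10 = 0.3 points, about a third of the half-width.

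A two-practice cross-arm merger removes one practice from each arm, so it adds nothing to f₁ − f₀ when the arms are of equal size. Any difference in exclusion rates would have to come from leavers.

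**The case against.** The strongest reply is that the leaver rule may describe data availability and not an analysis choice. The Data source section appears to place the extraction after follow-up, and nothing in the article says that CPRD supplies records for a practice that has since withdrawn. This stands. A reader might infer that the plan certainly discards complete primary-outcome data, but the document supports only the conditional form: it does so where CPRD can supply those data. Even so, unavailable data are missing clusters, to be counted by arm. They are not an exclusion criterion placed beside an intention-to-treat claim.

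It can also be said that the merger statements are compatible, with the specific rule qualifying the general one. That holds for same-arm mergers and splits, so it would be wrong to read the plan as excluding all mergers. It does not hold for cross-arm mergers, since removal is itself special treatment.

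Finally, the effect may be negligible. The protocol expects small numbers and says that practices will not know they are in the study, so no route is described by which the letter would change who leaves. This also largely stands. Only intervention practices receive correspondence, sent with CPRD's help, so an effect on leaving is conceivable, but nothing in the article shows one.

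**Conclusion.** The inconsistency is real and narrow. The article excludes randomised practices on post-allocation events while promising intention to treat, and it applies to the primary outcome an exclusion period of which 46–50% falls after that outcome is complete. That share assumes follow-up ends on 31 December 2021 and dispatch lies between mid-June and 1 July.

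A reader might go further and infer a materially biased primary result. The documents do not support that. The 0.1 to 0.3 point shifts rest wholly on assumed differences in exclusion rates between arms and assumed uptake gaps, and with equal rates and equal gaps the shift is zero. Precision is hardly touched: 0.98 to 1.01 points if 5% of practices are lost. The point concerns validity and consistency. It should be fixed before analysis, but it does not undermine the trial.

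**What to change.** Before analysis begins, reconcile the two sections as follows.

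1. Replace the two post-intervention exclusions with an availability rule for each outcome window. Every randomised practice with data to 30 September 2021 enters the primary analysis in its allocated arm, whatever happens to it later. The other outcomes use the end of their own windows.
2. For cross-arm mergers, assign children to the arm of their original practice where CPRD can identify it.
3. Treat practices that leave before 30 September, or whose data CPRD cannot supply, as missing clusters. Report their number and timing by arm. The availability rule does not recover these practices, so the text should not claim that every randomised practice is analysed.
4. Keep the present exclusion rule as a sensitivity analysis.

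The cost is a wording change and possibly a query to CPRD. Because the data have already been received, original practice codes or records of departed practices may be only partly recoverable. Keeping cross-arm mergers as allocated may slightly dilute the contrast between arms.
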